## Abstract

**Background:**

The implantable cardioverter defibrillator (ICD) is generally well accepted, but 25-33% of patients experience clinical levels of anxiety, depression, and impaired quality of life (QoL) following implantation. Few trials in ICD patients have investigated whether behavioral intervention may mitigate the development of these adjustment problems. We present the rationale and study design of the **WEB**-based distress management program for implantable **CAR**dioverter d**E**fibrillator patients (WEBCARE) trial.

**Methods:**

WEBCARE is a multi-center, multi-disciplinary, randomized, controlled behavioral intervention trial designed to examine the effectiveness of a web-based approach in terms of reducing levels of anxiety and device concerns and enhancing QoL. Consecutive patients hospitalized for the implantation of an ICD will be approached for study participation while in hospital and randomized to the intervention arm (n = 175) versus usual care (n = 175) at baseline (5-10 days post implantation). Patients will complete assessments of patient-centered outcomes at baseline, 14, 26, and 52 weeks after implantation. Patients randomized to the intervention arm will receive a 12-week web-based behavioral intervention starting 2 weeks after implantation. Primary endpoints include (i_i_) patient-centered outcomes (i.e., anxiety, depression, ICD acceptance, QoL); (i_ii_) health care utilization; and (i_iii_) cost-effectiveness. All primary endpoints will be assessed with standardized and validated disease-specific or generic questionnaires. Secondary endpoints include (ii_i_) cortisol awakening response; and (ii_ii_) ventricular arrhythmias.

**Discussion:**

WEBCARE will show whether a behavioral intervention using a web-based approach is feasible and effective in reducing anxiety and ICD concerns and improving QoL in ICD patients.

**Trial Registration:**

http://www.ClinicalTrials.gov. Identifier: NCT00895700.

## Background

Implantable cardioverter defibrillator (ICD) therapy is considered the treatment of choice for the prevention of sudden cardiac death (SCD) both in patients who have survived life-threatening arrhythmias (secondary prevention) and in patients at risk for these arrhythmias due to coronary artery disease and left ventricular dysfunction (primary prevention) [1]. The number of ICD implantations has risen considerably, since the first ICD was implanted in humans [2-4]. This increase in implantation rates can in part be attributed to expansion of the indications for ICD implantation to also include primary prevention, due to ICD therapy being superior to anti-arrhythmic drugs in the prevention of SCD in these high-risk patients [5-7].

Despite the medical benefits of ICD therapy, and the device generally being well accepted by the majority of patients [8], 25-33% of patients experience clinical levels of anxiety, depression, and impaired quality of life (QoL) following implantation [9-12]. These difficulties may be attributed to actual ICD shocks [13,14], but also to device-related concerns including fear of shocks [15,16], ICD advisories (i.e., a notification from ICD manufacturers that the hardware may potentially malfunction) [17], and the psychological make-up of the patient, including lack of optimism [18] and personality factors, such as the *distressed *(Type D) personality [11,12,19]. The prevention of the manifestation of psychological distress in ICD patients is important, given preliminary evidence that distress may increase the risk of ventricular tachyarrhythmias [20-22]. Hypercortisolemia, reflecting a dysregulation of the hypothalamus-pituitary-adrenocortical axis, may provide one of the mechanisms linking psychological factors to ventricular tachyarrythmias due to increased inflammation arising from chronic stress [23].

Preliminary evidence suggests that ICD patients benefit from psychological and behavioral intervention, with the largest effect being found in reductions of symptoms of anxiety and improved exercise capacity [24]. One intervention trial has also found a reduction in cortisol levels [25]. However, the number of large-scale intervention trials in ICD patients is scarce [24,26], with the majority of these trials having used a nurse-based approach, cognitive behavioral therapy as stand-alone therapy, or in combination with cardiac rehabilitation. A web-based intervention may be equally effective and have advantages over these more traditional forms [27]. Advantages of a web-based intervention include its low-threshold accessibility via the internet, which makes it logistically feasible for most patients to participate, as they do not have to take time off work, but can access the intervention at home in their own time. In addition, a web-based approach safeguards the patient's anonymity, and the patient avoids the stigma associated with traditional, face-to-face therapy. Such an approach may be particularly useful for patients with a Type D personality profile, who are at increased risk of adverse health outcomes, as they do not share their emotions in social interactions due to fear of rejection [28].

## Design

The **WEB**-based distress management program for implantable **CAR**dioverter d**E**fibrillator patients (WEBCARE) is a Dutch multi-center, multi-disciplinary, randomized, controlled behavioral intervention trial designed to examine the effectiveness and feasibility of a web-based approach in terms of reducing levels of anxiety and device concerns and enhancing QoL in ICD patients. The trial has been registered on http://www.ClinicalTrials.gov (NCT00895700).

### Study population and eligibility criteria

Consecutive patients (N = 350) hospitalized for the implantation of an ICD in three medical centers in The Netherlands will be approached for study participation while in hospital and randomized to the intervention arm (n = 175) versus usual care (n = 175) at baseline (5-10 days post implantation). Patients (i) being implanted with an ICD, (ii) between 18-75 years of age, (iii) speaking and understanding Dutch, (iv) with access to and ability to use the internet, and (v) providing written informed consent will be eligible to participate. Patients with a life expectancy less than 1 year, with a history of psychiatric illness other than affective/anxiety disorders, on the waiting list for heart transplantation, or with insufficient knowledge of the Dutch language will be excluded.

### Study procedure, randomization and follow-up

The study protocol will be approved by the medical ethics committees of the participating centers. The study will be conducted according to the Declaration of Helsinki, as amended in 2008 by the World Medical Association, and all patients will be informed orally and in writing about the purpose, rights, and possible benefits/risks of the study.

Patients will be invited to participate in the study while hospitalized for their ICD implantation. Patients responding positively to the invitation will be given the informed consent form and the baseline questionnaire package. In order to avoid measuring pre-operative stress, patients will be asked to complete the baseline assessment between 5 and 10 days (T_0_) after implantation. If the baseline questionnaire is not returned within 7 days, patients will receive a reminder telephone call. When the signed informed consent form and completed baseline assessments are received at the trial coordinating center, the coordinating center will randomize the patient either to the treatment arm or to usual care. There will be a separate randomization list for each participating hospital. The patient will be informed by telephone to which condition he/she has been randomized and the procedure for the rest of the study. If the patient is randomized to the internet intervention, he/she will receive a login and password in order to be able to access the intervention. The day of randomization will be the first day of the intervention period, with the duration of the intervention being 12 weeks. For both study conditions, the follow-up assessments will take place 14 (T_1_), 26 (T_2_), and 52 weeks (T_3_) post implantation. All randomized patients, irrespective of condition, will be followed until the scheduled study end. A schematic representation of the study design is shown in Figure 1.

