### Statistical analysis and power calculation

The trial is designed to show whether a web-based behavioral intervention is effective in improving patient-centered outcomes compared to usual care. The power analysis was performed in relation to anxiety as the primary endpoint, since anxiety is a pertinent outcome measure in ICD patients due to the unique feature of the ICD being able to provide a shock. With (i) an expected between group effect size of .30., based on a recent meta-analysis of web-based intervention for symptoms of anxiety and depression [36] and taking into consideration that our population consists partly of patients with subclinical anxiety and depression levels; (ii) alpha = 0.05; (iii) power = 0.80 (two-sided test), 350 patients are needed (i.e., 175 in each condition). Although we had a response rate of 82% in an earlier study [16,19], based on a more conservative response rate of 50%, 700 patients need to be approached.

The effectiveness of the intervention will be examined using the intention-to-treat principle, with the inclusion of all randomized participants in the statistical analysis regardless of whether they completed the intervention or the follow-up measurements. Missing data will be imputed using regression imputation techniques. Univariable and multivariable regression analyses (both linear and Cox proportional hazard regression analysis) and analysis of variance and analysis of covariance with repeated measures will be used to investigate the effect of the intervention on the endpoints. The type of regression analysis will depend on the endpoint in question. Demographic, clinical and psychological variables will be included in multivariable analyses in order to control for their potential confounding effects. A p-value < 0.05 will be used to indicate statistical significance. All data will be analyzed using SPSS 17.0 for Windows (SPSS Inc., Chicago, Illinois).

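### Patients are randomised from a separate list for each hospital, but the stated analysis names no hospital factor; adding one is a small, free gain in precision

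*Protocol article*

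**What the plan says.** Under Study procedure, randomization and follow-up, the protocol article says: "There will be a separate randomization list for each participating hospital". Study population and eligibility criteria places recruitment "in three medical centers in The Netherlands". Hospital is therefore a stratification factor with three levels. The article gives no block size or other balancing method.

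Statistical analysis and power calculation lists the methods as "Univariable and multivariable regression analyses (both linear and Cox proportional hazard regression analysis) and analysis of variance and analysis of covariance with repeated measures". Its only sentence on adjustment is: "Demographic, clinical and psychological variables will be included in multivariable analyses in order to control for their potential confounding effects". Neither hospital nor centre appears there as a covariate, a stratum or a random effect. The same section bases the sample size on anxiety, with "an expected between group effect size of .30", alpha 0.05, two-sided power 0.80, and 175 patients per arm.

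**The concern.** An analysis should normally reflect the way patients were randomised. Lists that balance the arms within hospital remove hospital differences from the treatment comparison. If the model has no hospital term, those differences still sit in the residual variance, so the reported standard error is larger than the true one.

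The adjustment sentence does not lead the analyst to correct this. Hospital is a design variable and does not fit naturally under demographic, clinical or psychological. The stated reason for adjusting, confounding, also points away from it, because a factor balanced by design does not confound. The univariable and ANOVA analyses, as named, have no hospital term.

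Hospital differences are conceivable. Under Intervention versus usual care, the control condition is whatever the three centres routinely provide, with home monitoring only where it applies. The article gives no figure for how much outcomes vary between hospitals. At stake is a little precision in a trial planned at 0.80 power with no margin.

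**Working it through.** **Inputs from the article (Statistical analysis and power calculation).** Standardised effect 0.30 (total SD = 1), alpha 0.05 two-sided, power 0.80, 175 per arm.

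**Assumed input.** r, the share of outcome variance lying between hospitals. The article does not give it, so it is shown as a range.

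**Step 1: reproduce the article's figure.** n per arm = 2 × (1.960 + 0.842)² / 0.30² = 174.4, rounded up to 175, so 350 in total, as stated. Power at 175 per arm is 0.801 by the normal formula (0.799 by the exact t-test).

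**Step 2: standard errors with arms balanced within hospital.**
- Reported without hospital: SE_u = √(2/175) = 0.1069.
- True, and reported with hospital in the model: SE_t = √((1 − r) × 2/175).
- Overstatement: SE_u / SE_t = 1/√(1 − r).

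**Step 3: error rate and power.**
- Type I error without hospital = 2 × [1 − Φ(1.960 × SE_u/SE_t)].
- Power without hospital = Φ((0.30 − 1.960 × SE_u)/SE_t).
- Power with hospital = Φ(0.30/SE_t − 1.960).

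For example, at r = 0.05, SE_t = 0.1042. Power without hospital is Φ((0.30 − 0.2095)/0.1042) = Φ(0.868) = 0.807. Power with hospital is Φ(2.879 − 1.960) = Φ(0.919) = 0.821.

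| r (assumed) | SE ratio | Type I error without hospital | Power without hospital | Power with hospital |
|---|---|---|---|---|
| 0 | 1.000 | 0.050 | 0.801 | 0.801 |
| 0.02 | 1.010 | 0.048 | 0.804 | 0.809 |
| 0.05 | 1.026 | 0.044 | 0.807 | 0.821 |
| 0.10 | 1.054 | 0.039 | 0.814 | 0.841 |

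For r = 0.02, 0.05 and 0.10, the power gain from including hospital is about 0.5, 1.4 and 2.7 percentage points.

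**Step 4: simulation.** 20,000 trials per setting, with assumed hospital sizes of 120, 120 and 110 and each list exactly balanced. At r = 0.05, type I error was 0.042 without hospital and 0.048 with it; power was 0.802 and 0.817. At r = 0.10, type I error was 0.038 and 0.048; power was 0.809 and 0.837. Direction and size agree with the formulas.

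**Step 5: scope.** The formulas treat one cross-sectional comparison of a continuous outcome in which the whole hospital share stays in the residual. Nothing was calculated for the Cox model.

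**The case against.** The strongest reply is that this is only silence. The adjustment sentence names open categories and itemises no covariate at all. The article condenses a fuller protocol, and neither that protocol nor an analysis plan is shown. A reader might infer that hospital has been ruled out of the analysis, but the text does not support that: it does not name hospital, and it does not say that hospital will be omitted. What remains is that the article does state which kinds of variable will be adjusted for and why, and hospital fits neither the kinds nor the reason.

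Second, a reader might infer that the standard error is bound to be wrong. That requires balance within each list, and the article mentions no blocking. With simple randomisation inside each list, the unadjusted standard error would be valid, although adjustment would still gain precision if hospital predicts outcome. Separate lists have little purpose unless they balance the arms, so balance is the natural reading, but it is an inference. This objection stands as a condition on the result.

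Third, the planned repeated-measures analyses blunt the effect. In a group-by-time test, stable hospital differences in level cancel within patients. A baseline score used as a covariate absorbs hospital differences already present at baseline. The article does not say which test is primary. This also stands, and it makes the figures in the table upper bounds.

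Fourth, it is tempting to set the power with hospital (0.81, 0.82, 0.84) against the planned 0.80. That overstates the gain, because under balanced lists the unadjusted test also gains a little power. The fair comparators are 0.804, 0.807 and 0.814.

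**Conclusion.** The point holds as a low-severity improvement. Randomisation is stratified by hospital, and the stated adjustment set does not name hospital. If the lists are balanced and hospital predicts outcome, an analysis that follows the text as written would overstate the standard error by at most about 1%, 3% or 5% when hospitals account for an assumed 2%, 5% or 10% of outcome variance. It would forgo at most about 0.5, 1.4 or 2.7 points of power.

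A reader might infer from a mismatch between design and analysis that the trial's conclusions are at risk. The documents do not support that. The error is on the conservative side, the treatment estimate for continuous endpoints is not biased, false positives are not inflated, power by the normal formula stays above 0.80, and the sample size of 350 is unaffected. The gap in the text is certain. The size of the loss depends on r, for which the article gives no value.

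**What to change.** Add one sentence to the analysis section, or confirm it in the analysis plan before outcome data are seen: hospital (three levels), as the factor by which randomisation was stratified, enters the arm comparisons of the continuous endpoints as a fixed factor, at a minimum in the primary anxiety model. Give the reason as reflecting the randomisation, separately from the confounding rationale. It would also help to state whether the lists are blocked.

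The cost is two degrees of freedom out of about 350, with no extra patients and no extra data collection. Stratifying the Cox model for ventricular arrhythmias by hospital would be consistent with this, but it is optional, because no gain was calculated for it.

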### Intervention versus usual care

Patients randomized to the treatment arm will receive an internet-based intervention starting 2 weeks after implantation. They will receive a username and password to access the intervention via the web. Every week an automated email will be sent to the participants to explain the contents and exercises for the coming week. All the information, as well as the exercise forms, will be downloadable from the website in case participants prefer to read the information on paper. Master's level psychology students, trained and supervised by psychologists will provide feedback on the completed exercises. This feedback is not meant to be therapeutic; it will be directed toward mastering the problem-solving strategies. The maximum amount of time the psychology students should spend on feedback will be 60 minutes per participant. The components of the intervention are presented in Table 2. The intervention has to be completed within 12 weeks, as we learnt in an earlier trial that one session a week is too fast a pace for most people. A typical session takes about 30 minutes and consists of an introduction, a discussion of the previous lesson's homework, new theory and homework for the subsequent week. The sessions are designed to be followed on a weekly or two-weekly basis. These time indications may vary among users. Besides the sessions, the participants have several resources at their disposal: a homework station, extra information, reading tips, useful links, and addresses for additional help. Patients randomized to the usual care arm will receive care as it is standardly offered to ICD patients in the three centers, comprised of an information booklet about ICD treatment, standard clinical follow-up visits, and home monitoring of the device (if applicable).

**Table 2 T2:** Components of the 12-week web-based intervention

*Components*	*Topics dealt with*
**▪ Psycho-education about the ICD**	▪ Emotional reactions to ICD therapy
**▪ Problem-solving skills**	▪ Which aspects of ICD therapy may lead to distress
**▪ Cognitive restructuring**	▪ How to deal with shocks
	▪ Disease-specific issues and fears
**▪ Relaxation training**	▪ How to prevent the avoidance of activities
**▪ Personalized feedback by a therapist via the computer**	▪ Interpretation of bodily symptoms
	▪ How to cope with uncertainty
	▪ Help-seeking behaviour
	▪ How to cope with stress

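### The stated start points for randomisation and intervention conflict, and T1 at 14 weeks after implantation can fall before the 12-week intervention period ends

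*Protocol article*

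**What the plan says.** **Randomisation.** Study population and eligibility criteria, like the Methods paragraph of the abstract, has patients "randomized to the intervention arm (n = 175) versus usual care (n = 175) at baseline (5-10 days post implantation"). Study procedure, randomization and follow-up gives a different trigger: "When the signed informed consent form and completed baseline assessments are received at the trial coordinating center, the coordinating center will randomize the patient". Days 5 to 10 are there the window for filling in the forms: "patients will be asked to complete the baseline assessment between 5 and 10 days (T_0_) after implantation". On late forms the section says: "If the baseline questionnaire is not returned within 7 days, patients will receive a reminder telephone call". It gives no latest date for return or for randomisation.

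**Start of the intervention.** Study procedure states: "The day of randomization will be the first day of the intervention period, with the duration of the intervention being 12 weeks". Intervention versus usual care states: "Patients randomized to the treatment arm will receive an internet-based intervention starting 2 weeks after implantation". The abstract also uses the 2-week start.

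**Assessments.** All follow-up is counted from implantation: "For both study conditions, the follow-up assessments will take place 14 (T_1_), 26 (T_2_), and 52 weeks (T_3_) post implantation". The footnote to Table 1 repeats these weeks. No assessment is tied to randomisation or to the end of the intervention.

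**The concern.** There are two linked problems. First, a coordinating centre cannot follow all the timing statements at once: a patient randomised on days 5 to 10 whose intervention begins that day does not begin 2 weeks after implantation. Second, T1 is the assessment placed at the nominal end of treatment, but its date is tied to implantation, while one of the start rules ties the intervention to the arrival of paperwork. If the paperwork is slow, T1 is due while the 12-week period is still running.

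At stake is what T1 measures. It would be a post-treatment result for some intervention patients and a late mid-treatment result for others, depending on how quickly they returned their forms. That weakens T1 as an end-of-treatment contrast and makes it harder to interpret.

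**Working it through.** **Inputs, in days from implantation**
- Baseline forms completed: days 5 to 10 (Study procedure).
- Intervention length: 12 weeks = 12 × 7 = 84 days (Study procedure).
- Alternative start: 2 weeks = day 14 (abstract; Intervention versus usual care).
- T1 = 14 × 7 = day 98; T2 = 26 × 7 = day 182; T3 = 52 × 7 = day 364 (Study procedure; Table 1).
- R = day of randomisation.

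**Step 1: the article's own figure.** A start on day 14 gives an end on 14 + 84 = day 98, which is T1. The 14-week assessment is therefore the 2-week start plus the 12-week period, with nothing to spare.

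**Step 2: can the rules hold together?** If R is between 5 and 10 and the intervention starts on R, the start is 4 to 9 days before day 14. If the start is day 14 and equals R, then R is outside days 5 to 10. One statement must give way.

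**Step 3: T1 when randomisation starts the intervention.** The period ends on R + 84. T1 precedes that end when 98 < R + 84, that is, when R > 14. The shortfall is R − 14 days.

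| R | End of period | T1 minus end (days) | Days of period elapsed by T1 | T2 minus end (days) |
|---|---|---|---|---|
| 5 | 89 | +9 | 84 of 84 | 93 |
| 10 | 94 | +4 | 84 of 84 | 88 |
| 14 | 98 | 0 | 84 of 84 | 84 |
| 17 | 101 | −3 | 81 of 84 | 81 |
| 21 | 105 | −7 | 77 of 84 | 77 |
| 28 | 112 | −14 | 70 of 84 | 70 |

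Values of R above 10 are assumptions, since no latest date is given. At R = 17 the shortfall is 3/84, about 4% of the period; at R = 28 it is 14/84, about 17%.

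**Step 4: can R exceed 14?** Yes. Forms completed on day 10 need only take more than 4 days to reach the centre and be processed. A reminded patient may be later still. If the 7 days before the reminder run from the completion window (an assumption), reminded patients are randomised after day 5 + 7 = 12 to day 10 + 7 = 17.

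**Step 5: later assessments.** In every case tabulated T2 falls 70 to 93 days after the end of the period, and T3 is 182 days after T2. Only T1 is affected.

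**The case against.** Much can be said for the plan. The 2-week start may be shorthand: forms completed by day 10 plus a few days for return come to about two weeks, and a journal article condenses. The schematic of the procedure (Figure 1) is not available here and might clarify the sequence. This softens the contradiction but does not remove it, because Study procedure gives an exact rule. If the two weeks are only approximate, an assessment at exactly 2 + 12 weeks needs slack that it lacks.

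Twelve weeks is also a maximum. Sessions are weekly or two-weekly, and some patients may finish early, so days remaining are not the same as treatment missed. That stands, although the article itself says that one session a week is too fast for most people. When the 7 days before the reminder begin is not stated either, so late randomisation is possible but its frequency is unknown.

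Counting from implantation is a defensible choice, since it holds recovery time constant across patients.

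A reader might infer more than the article supports:
- *Bias between arms.* The delay arises before allocation, so it is balanced in expectation, and the assessment calendar is the same in both arms.
- *A definite loss of power.* This would need the share randomised late, the way benefit builds up, and T1 as the sole primary time point. The article gives none of these, and it plans repeated-measures analyses as well as regression.
- *A mis-set clock for arrhythmias.* The article states no time origin for that analysis, and an article may leave it to the analysis plan.
- *Baseline measured outside its window.* Late return need not mean late completion, and a cut-off may stand in the full protocol.

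**Conclusion.** The point holds in two parts. The statements on when patients are randomised and when the intervention begins are incompatible as written. And if randomisation is the first day of the intervention, T1 precedes the end of the 12-week period for anyone randomised after day 14, one day for each day of delay.

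The size per patient is days to about two weeks for randomisation up to day 28, an illustrative limit. The number of patients affected cannot be known from the article. The consequence is some dilution and variable exposure at T1. The comparison between arms remains unbiased on this account, T2 and T3 still follow the intervention, and the sample size is untouched. The conclusion rests on reading the 12 weeks as the full period allowed and on T1 being taken on its stated date, since no assessment window is given.

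**What to change.** 1. Reconcile the abstract, Study population and eligibility criteria, Study procedure, and Intervention versus usual care, so that they give one rule for when randomisation takes place and one for when the intervention period begins. Which rule is right is for the investigators to decide.
2. Schedule T1 by the same rule in both arms, counted from randomisation, so that it falls no earlier than the end of the 12-week period.
3. Record the actual number of days from randomisation to each assessment, so that exposure at T1 can be described.

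The cost is amendment wording and a change to the mailing schedule. The downside is that time since implantation at T1 would vary by days to a few weeks for patients whose forms come back late, giving up some of the uniformity that the present calendar provides.
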